**Follow-up assessments**

1. Research Workers also have the responsibility to remind participants/family members and clinical team that blindness must be maintained – this is particularly important at the follow-up assessment. To this end,
   1. Standard letters will be sent to participants (from the contacts database) during the follow-up period with a newsletter, Christmas cards, alerting them to the fact that their baseline assessment is due, confirming their appointment details etc which state, that the Research Worker cannot know if the participant developed a JCP or not.
   2. When phoning and at the assessment, the Research Worker should restate that they cannot know if the participant developed a JCP or not.
2. Site leads are responsible for ensuring that data that needs to be collected from electronic systems/case notes (admissions and contact data) shall be requested in electronic form from centralised IT systems. RW should not access electronic systems at the follow-up assessment as the JCP will be attached and their may be a flag/alert regarding the presence of a JCP.
3. Where feasible, the administrator’s number should be given out to participants instead of the Research Workers or facilitator’s individual numbers. The administrator can then direct messages and this will help to avoid situations where a participant mistakenly calls the Research Worker looking for the facilitator.

**In case of blind breaches:**

1. SF and the site lead should be notified via email
2. SF will complete a form to record the breaching
3. A different Research Worker at the site will take over and complete the assessments Where this is not possible, the unblinded Research Worker should co-rate with SF.

**Success of blinding**

At follow-up, each Research Worker will be asked to guess which intervention arm a participant is in.

# Appendix 5 – Analysis Plan.

**Analysis Plan Draft 2**

**8/26/2008**

Individual-level single-blind RCT of Joint Crisis Plans (JCPs) compared with a ‘treatment as usual’ control condition for people with a history of relapsing psychotic illness in Birmingham, London and Manchester. There will be one follow up point at 18 months after the completion of the JCP.

Allocation will be by randomised permuted blocks of randomly varying block size (sizes 2 and 4), with equal allocation to the two arms, stratified by centre. The Mental Health & Neuroscience Clinical Trials Unit (MH&N CTU) will perform the allocations.

**The total to be recruited is 540, or 180 per site (which includes 48 who also have qualitative assessments after the 18 month follow-up).**

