**5.1 Randomisationprocedure and methods to minimise bias**

A list, generated by Clinical Studies Officers from the Mental Health Research Network, will be maintained by the Study Co-ordinating Centre of all service users at each local site fulfilling the inclusion and exclusion criteria for the study. Each eligible person will then be approached by a member of the research team and invited to participate in the study, thus eliminating selection biases. A randomisation list of those eligible and consenting, stratified by centre, will be prepared using randomised permuted blocks of randomly varying block size, with equal allocation to the two arms. The randomisation will be managed by an independent system that will provide random allocation to all sites when provided with subject identification number, and so ensure the concealment of allocation of service user status in the two arms of the trial. Confirmation of eligibility and consent, and minimal baseline data will be obtained prior to randomisation.

The co-ordinating centre will scrutinise the implementation of the JCP intervention across sites to ensure fidelity and comparability of the intervention are preserved, using a rating scale for this purpose along with analysis of taped interviews.

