# The Intervention

**6.1 Experimental Intervention:** At each site, a trained and clinically experienced Facilitator will organise a meeting with each service user randomised to receive a JCP. The Facilitator will introduce the JCP ‘menu’ (a list of topics to be considered for inclusion in the JCP) to each service user. He/she will then organise a meeting between the service user, team consultant psychiatrists or other psychiatrist, and the Care Co-*ordinator/ treating doctor’,* when the JCP contents will be finalised. The service user is encouraged to bring a carer or friend to act as an advocate. The JCP contains: information on early warning signs of relapse and advance treatment statements; contact details of primary and secondary care staff for routine and emergency care; details of medication; psychiatric and physical diagnoses; allergies; and details of who will have a copy of the JCP. The Facilitator produces a typed version of the JCP, computer-generated to allow replacement and updating, and it will also be included on computerised patient information systems where these are in routine use by the services. Copies will be sent to all those whom the service user specifies.

**6.2 Control intervention.** After careful consideration, we have chosen to use a treatment as usual (TAU) control condition, as this provides a fair comparison with routine clinical practice, and will answer the question of whether JCP use is superior to current standard care. TAU includes, as a part of the Care Programme Approach (CPA), the need for service users to receive written copies of their care plan3, including a ‘crisis contingency plan’, as indeed was the case in our recent exploratory trial. We expect that the CPA arrangements in secondary care, and the new 2006 Quality Outcome Framework (QOF) to have a care plan documented in primary care case records, will be applied equally by routine services to intervention and control groups, and there is little evidence for differential QOF implementation between practices. We shall assess the content of the Care Programme Approach of all participants at baseline and follow-up.

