# Assessments

**7.1. Primary outcome.**

**Primary:**

1. Proportion of service users admitted or otherwise subsequently detained under an order of the Mental Health Act during the follow-up period. MHA data will be gathered from and validated between the following sources: case notes, the local Patient Administration System, Mental Health Act Office data, and interviews of service users and Care Co-ordinators.

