**Secondary:**

1. Cost as measured by the Adult Service-Use Schedule (see section 3.11)
2. Perceived coercion (Admission Experience Inventory)48
3. Engagement with mental health services (Engagement and Acceptance Scale49 and Service Engagement Scale 60
4. Therapeutic relationship for service users and staff (Working Alliance Inventory)50

In addition socio-demographic data will be collected at baseline, and social and functional clinical descriptors (baseline and follow-up) will be gathered along with the Global Assessment of Function51. We shall also record: involuntary transport to hospital under the MHA, police involvement in admission, incidents of violence, incidents of self harm, and criminal justice system involvement. In addition we shall conduct systematic analyses of the content of these JCPs in terms of treatment preferences, instructions, information, and consent or refusal of interventions. Ethnicity will be described using ONS categories as they have been thoroughly tested and are known to be acceptable to the majority of the population52. Additionally, socio-demographic data and length of practice data will be collected for care co-ordinators.

To ensure the accurate reporting of the representativeness of the trial sample, we will collect basic demographic data (age, gender, diagnosis, ethnicity and last hospital admission) on those who refused to participate in the trial.

At follow-up we will contact all participants who originally participated in the trial. Intervention participants who refused to complete a Joint Crisis Plan, will be contacted via a letter to clarify their wishes for any further involvement in the trial.

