#### 7.2 Qualitative evaluation

Qualitative studies will be carried out to explore the processes through which JCPs achieve change in practice. Pilot work suggests they have direct and indirect effects. Negotiating JCP content may clarify treatment issues and build consensus between service users and staff. However effects on trust (based upon the approach of Mechanic)53, service user engagement in the process of care including shared decision making32, changes to service user self esteem, and empowerment, clearer channels of communication between all parties, changes to staff risk perception and/or changes within the culture of the mental health service may also be important. Focus groups, a potentially more enabling setting for vulnerable users to express their views than individual interviews, will be used to examine people’s experience of the JCP. The dynamic interaction of the group can also provide insights into attitudes, perceptions and opinions and dissent between participants can clarify beliefs and reveal underlying assumptions. The important ‘break characteristic’ used in data analysis will be whether service users with a JCP were subject to coercion (MHA use). 18 focus groups (6 groups in each site) will run 18-21 months after entry to the study.

Separate service user and health professional focus groups with service users who have or have not been coerced as defined will be followed, usually one week later, by a combined subset of the service users and health professionals who attended the separate groups. We expect to involve 16 service users in each geographical site and a similar number of professionals involved in the development of the JCP with the service user. This tripartite technique has been used with good effect by one of the applicants59. Focus group topic guides will be developed from a literature review and include the themes discussed above54-56. Combined groups will additionally explore the roles and responsibilities of service users and health care professionals in relation to the use of the JCP and the influence on and impact of the culture of mental health services. **If there are insufficient numbers to arrange focus groups in any of the sites, individual interviews will be conducted to collect detailed information of individuals’ experiences of the intervention.**

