**8.2. Analysis plan**

The principal analysis of effectiveness will compare the primary and secondary outcome measures at 18 months, combined over centres. The proportions admitted to hospital under a section at follow up will be compared between randomisation groups using logistic regression controlling for centre. Other (continuous) outcomes such as therapeutic alliance and engagement with mental health services will be analysed using analysis of covariance controlling for baseline (pre-intervention) measures and centre. Number of admissions will be analysed using Poisson regression, and time to first admission using survival analysis. Bed-days and other very skewed data will be analysed using bootstrapping to obtain confidence intervals and p-values70. Short scales will be analysed using ordered logistic regression. An intention-to-treat analysis will be applied in the first instance (i.e. analysing all available data from service users as randomised). Time trends in measures available at baseline and two time points will be analysed using methods for longitudinal data such as random effects regression. Sensitivity analyses will be performed to assess the influence of loss to follow-up and refusals, including imputation of missing baseline values from the within-centre means; multiple imputation of follow up values (where feasible from other variables) and CACE analyses65. (Full analysis plan is in Appendix 4)

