**Measures**

B=Baseline, FU Follow-up at 18 months post baseline

**Colleagues with as special interest in the outcome scales are noted below in case of queries regarding scoring or interpretation. This is a preliminary suggestion and subject to change – please contact SF or ML if you prefer not to be the ‘expert’ for the particular scale or would rather take on another (or no) scale.** **We need someone to take an interest in the Engagement and Acceptance scale**

| **Primary/secondary outcomes** | **Standardised measure** | **Source** | **Time** |
| --- | --- | --- | --- |
| MHA use (primary) | Routine hospital datasets | Admin. Records + Patient Information Records using Admissions Proforma* | B FU |
| Informal admissions | As above | As above | B FU |
| Recovery Style  (MB) | Recovery Style Questionnaire | Self-report** | B FU |
| Perceived coercion  (GS) | Treatment Experience Survey (Community) | Self-report (based on MacArthur AES) ** | B FU |
| Engagement with care  (?) | Engagement and Acceptance Scale | Staff-rated | B FU |
| Therapeutic relationship  (JS) | Working Alliance Inventory | Self-report**  and Staff-rated | B FU |

*To be collected for all patients including dropouts (refusals or uncontactable) unless patient specifically requests otherwise.

** Interviewer helps in cases of literacy problems only

| **Other outcomes*** | **Standardised measure** | **Source** | **Time** |
| --- | --- | --- | --- |
| Functioning  (SF) | Global Assessment of Function (GAF) | Rater | B FU |
|  |  |  |  |
| Involuntary transport to hospital  under the MHA | Admissions Proforma | Case notes | B FU |
| Police involvement in admission | Admissions Proforma | Case notes | B FU |
| Incidents of violence and sef-harm  (MB?) | COMMAND questionnaire | Interview | B FU |
| Criminal justice system involvement  (SB/BB) | Crimson AD-SUS | Interview | B FU |

Is GAF an outcome as such or is it a predictor?

| **Socio-demographic data*** | **Standardised measure** | **Source** | **Time** |
| --- | --- | --- | --- |
| OPCRIT diagnosis  (MHRN CSO at each centre) | OPCRIT | Case notes | Eligibility (prebaseline) |
| Centre |  |  | B |
| Gender | Crimson Sociodemographics | Interview | B |
| Ethnic group (W, BA, BC, other) | Crimson Sociodemographics | Interview | B |
| Age | Crimson Sociodemographics | Interview | B |
| Clinical diagnosis  (SF) | Crimson Sociodemographics | Case notes (text -codes to be decided) | B |

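### The Analysis Plan appendix times the only follow-up from JCP completion, which contradicts 18 months post baseline elsewhere and cannot be applied to controls or to participants who refuse a JCP

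*Protocol*

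**What the plan says.** The protocol gives two anchors for its single follow-up.

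- **Analysis Plan appendix (headed Appendix 5), opening paragraph:** "There will be one follow up point at 18 months after the completion of the JCP".
- **Outcome measures table in section 7.2, and the Measures table of the same appendix:** "B=Baseline, FU Follow-up at 18 months post baseline". The appendix table applies this label to MHA use, marked as primary, and its footnote has those records collected for dropouts too, unless the patient asks otherwise.

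The primary outcome (section 7.1, repeated in the appendix) is "Proportion of service users admitted or otherwise subsequently detained under an order of the Mental Health Act during the follow-up period". Neither place dates the start or end of that period. Section 8.2 adds "The principal analysis of effectiveness will compare the primary and secondary outcome measures at 18 months, combined over centres", without an anchor.

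Two other places bear on the question. Section 8.3 refers to the proportion sectioned over an 18-month follow-up period. Section 7.2 describes interviews about intervention participants' experience in the 18-month follow-up, and includes JCP development in that experience.

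On who has which date: section 6.2 states "we have chosen to use a treatment as usual (TAU) control condition"; section 7.1 foresees that "Intervention participants who refused to complete a Joint Crisis Plan, will be contacted via a letter"; and section 5.1 states "Confirmation of eligibility and consent, and minimal baseline data will be obtained prior to randomisation".

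**The concern.** One follow-up point cannot lie 18 months after two different events. JCP completion must come later than baseline. The baseline assessment is finished before randomisation, and the facilitator then meets the service user and arranges a further meeting at which the plan is finalised (section 6.1 and the appendix on blinding).

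The JCP date also exists only for intervention participants who complete a plan. Controls and JCP refusers have none, and no substitute date is offered, yet the plan analyses everyone as randomised.

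This matters because the primary outcome is at least one section during the period, so the proportion rises with time at risk. Section 8.2 sends the analyst to this appendix for the full plan. If its opening sentence were used where a JCP date exists and the baseline clock where it does not, time at risk would differ by arm.

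**Working it through.** **1. The plan's own figures, which assume one 18-month window in both arms.**

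Rate scaling (section 8.1): 26% over 15 months at a constant hazard gives 1 − 0.74^(18/15) = 30.3%, which agrees with the stated 30%.

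Sample size: for 30% against 15%, two-sided alpha 0.05 and 90% power, the standard two-proportion formula gives

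n = [1.960 × √(2 × 0.225 × 0.775) + 1.282 × √(0.30 × 0.70 + 0.15 × 0.85)]² / 0.15² = 161.

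The continuity correction raises this to 174 per arm, the stated figure. The calculation is sound and is not part of this point.

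**2. Who can be given each anchor.**

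| Participants | Baseline date | JCP completion date |
|---|---|---|
| Controls | yes | none |
| Intervention, JCP refused | yes | none |
| Intervention, JCP completed | yes | yes, after randomisation |

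Only the baseline anchor covers all rows.

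**3. Size if the two anchors are mixed.** Suppose everyone is counted from baseline, JCP completers to 18 months after their JCP and the others to 18 months after baseline.

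Inputs: 30% over 18 months (section 8.1); constant hazard (assumption); no true effect; all intervention participants complete a JCP (assumption, which gives an upper bound for each lag); lag L from baseline to JCP of 3 months, range 1 to 6 (assumption, as the documents give no figure).

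Risk over T months = 1 − 0.70^(T/18), with T = 18 + L in the JCP arm.

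| L (months) | T in JCP arm | JCP arm | Control | Difference (points) |
|---|---|---|---|---|
| 1 | 19 | 31.4% | 30.0% | +1.4 |
| 3 | 21 | 34.0% | 30.0% | +4.0 |
| 6 | 24 | 37.8% | 30.0% | +7.8 |

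If only a fraction c completes a JCP, and completers have the same hazard as the rest, the difference is c times the value shown.

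**4. What this does to the test.** With 270 per arm and a pooled two-proportion z test, the nominal 5% rejection rate with no true effect becomes about 6%, 17% and 49% at lags of 1, 3 and 6 months, mostly against the JCP.

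For the planned effect, let the control hazard apply until JCP completion and the 15% hazard afterwards. The JCP-arm rate under mixed windows is 1 − 0.70^(L/18) × 0.85, and under a common baseline window it is 1 − 0.70^(L/18) × 0.85^((18−L)/18).

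| L (months) | Power, common window from baseline | Power, mixed windows |
|---|---|---|
| 1 | 97.5% | 96% |
| 3 | 92% | 78% |
| 6 | 74% | 30% |

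Power at the design rates of 30% and 15% is 98.8%. The drop from there to the middle column comes from the delay before a JCP can act and would occur with a correct window. Only the gap between the two columns belongs to the mixed anchors.

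**The case against.** The strongest reply is that the protocol already has a usable rule. The baseline anchor appears twice, once in the same appendix and directly against the primary outcome. Section 8.3 gives the period as 18 months. The interviews in section 7.2 treat JCP development as part of follow-up, so follow-up has begun before the JCP is complete. On this view one descriptive sentence, in an appendix marked as a second draft and dated 2008, is out of step with the rest. That stands as evidence of intent. It does not remove the sentence from the current text.

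Three stronger readings are tempting, and the documents do not support them.

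- *Controls have no start date.* This is true only under the opening sentence of the appendix. Under both tables, every participant is anchored at baseline.
- *The bias could equally favour the JCP.* A reader might start the JCP arm at JCP completion and stop it 18 months after baseline. At a 3-month lag that leaves 15 months and 1 − 0.70^(15/18) = 25.7% against 30.0%. No passage describes such a window: it joins a start inferred from one sentence to an end taken from another. If counting ran from JCP completion to 18 months later, the window would be 18 months and the same model would give 30.0% in both arms.
- *The plan prescribes unequal windows, or abandons intention to treat.* The opening sentence fixes a follow-up point and does not say when counting of MHA events begins. Everyone would still be analysed as randomised. The fault would be unequal ascertainment between arms.

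The focus-group timing, "18 focus groups (6 groups in each site) will run 18-21 months after entry to the study", is not a separate defect. It fits the baseline clock and becomes awkward only under the JCP clock.

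**Conclusion.** The point holds as an internal contradiction that reaches the window of the primary outcome. The opening sentence of the Analysis Plan appendix conflicts with section 7.2 and with the appendix's own Measures table, sits badly with section 8.3, and cannot be applied to controls or JCP refusers.

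If it were applied to JCP completers only, the bias would run against the JCP. It would be at most about 4 percentage points at a 3-month lag (1.4 to 7.8 points for lags of 1 to 6 months), against a target difference of 15 points. These figures rest on a constant hazard, full JCP completion and a lag that the documents do not give, so they illustrate what the text leaves open and do not predict the trial's result. The planned 174 per arm stands.

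**What to change.** Replace the opening sentence of the appendix with wording such as: *There will be one follow-up point, 18 months after baseline, for every randomised participant in both arms, whether or not a JCP is completed; the primary MHA outcome is counted over those same 18 months.*

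The randomisation date, which follows the baseline assessment, would serve equally well if used throughout. What matters is one date that every randomised participant has and one window length for both arms. Carry the same date into the primary outcome definition in section 7.1 and the appendix, the cut-off for record extracts, the scheduling of follow-up interviews, and the origin for time to first admission.

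For the primary outcome the cost is wording only, because baseline and randomisation precede any JCP for everyone and MHA use is taken from administrative records. If any interviews have already been timed from JCP completion, their actual timing should be reported by arm.

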Bias in the recruitment and randomisation process will be avoided by having randomisation done centrally by an independent system, and hence concealment maintained from the investigators, and by keeping a log of all service users randomised and including them all in the analysis. Research workers, who will collect outcome data, will be blinded to the allocation. Some outcome data (in particular the primary outcome) will be obtained from staff, case notes, and administrative sources, even for service users lost to follow-up interview. Bias in the outcome data will also be minimised by the use of standardised objective assessments and by blinding the researchers as far as possible to service user allocation. In addition there will be specific instructions to participants and clinical teams not to disclose treatment details; along with separate administrative functions and office space with clear protocols and protected data storage in line with Good Clinical Practice Guidelines (full blinding procedures available in Appendix 3). As is common in effectiveness trials46, every effort will be made to maximise the single blindness of research raters, whose ‘best guesses’ of service user status will be assessed to test whether their blindness is maintained*.*

Likewise, demographic information of trial refusers will be collected to accurately assess the representativeness of the final trial sample and to assess whether there were any biases in the recruitment of trial participants..

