**Randomisation**

1. It is the responsibility of the Research Workers to collect all baseline data from participants and electronic patient systems ***before*** alerting the Coordinator that the participant is ready to be randomised.
2. Research Workers will not be involved in the randomisation of subjects, other than alerting the Coordinator that a participant is ready to be randomised. After fully completing the baseline assessment interview, Research Workers will inform [name] via the dedicated form in the data entry database that the participant is ready to be randomised. SF will then access the online randomisation service hosted by the IOP CTU and enter in the participants details. The Research Workers will receive an email alerting them to the fact that their participant has been randomised. At this point, the Research Worker will then enter that they have received confirmation of randomisation in the data entry database. The baseline data for this individual will then be blocked.
3. After the randomisation confirmation has been received by the Research Worker and they have entered this into the data entry database, Research Workers should not look at the participants clinical notes again.
4. The JCP facilitator at each site will receive an email informing them that a participant has been randomised and to which intervention arm. It is the responsibility of the facilitator at each site to ensure that the Research Workers do not see this correspondence.
5. The facilitator at each site will then inform both the control and intervention groups of the allocation. It is the responsibility of the facilitator to ensure that the Research Workers do not see this correspondence.
6. When discussing the allocation with the participant, the facilitator will give the participant the SF’s or local Trial administrator’s number in case he or she wishes to discuss the allocation further at a later date.
7. Facilitator to file randomisation notification emails and other identified information regarding intervention arm, in locked filing cabinet separate to Research Worker files

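### Printed block sizes of 2 and 4, with a site facilitator who sees every allocation in both arms, leave the claimed allocation concealment not fully secured

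*Protocol*

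**What the plan says.** Appendix 5 (Analysis Plan) of the protocol, in its opening paragraphs, gives the allocation scheme: "Allocation will be by randomised permuted blocks of randomly varying block size (sizes 2 and 4), with equal allocation to the two arms, stratified by" (the only stratification factor is centre). It also gives the length of each list: "The total to be recruited is 540, or 180 per site". Section 5.1 describes the same scheme without the sizes: "stratified by centre, will be prepared using randomised permuted blocks of randomly varying block size, with equal allocation to the two arms".

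Appendix 4 (Risks to blinding), under Randomisation, says who learns the result. Step 4: "The JCP facilitator at each site will receive an email informing them that a participant has been randomised and to which intervention arm". Step 5: "The facilitator at each site will then inform both the control and intervention groups of the allocation".

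Section 5.1 makes three claims of protection. The independent system will "so ensure the concealment of allocation of service user status in the two arms of the trial". Bias is avoided by "having randomisation done centrally by an independent system, and hence concealment maintained from the investigators". On recruitment it says: "Each eligible person will then be approached by a member of the research team and invited to participate in the study, thus eliminating selection biases".

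(Appendix numbers here follow the headings in the body of the protocol, which differ by one from its contents page.)

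**The concern.** A central system hides the list itself. It does not stop someone from inferring the next entry from past entries when blocks are very short and their sizes are known. Two and four are the smallest sizes that 1:1 blocks can have. With centre as the only stratification factor, one person at each site can follow the whole list for that stratum in order.

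Section 5.1 does not say which team members approach eligible people. No section keeps the facilitator, the site lead or the Coordinator out of identifying, approaching or ordering participants. Two further provisions in Appendix 4 (Intervention) matter. Research Workers are asked, where possible, to tell facilitators of their coming assessments, and this is not limited to follow-up. Team meetings may also have a part, without Research Workers, in which individual participants are discussed. The written safeguards are aimed at Research Workers learning past allocations; none addresses prediction of future ones.

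At stake is selection bias: who is approached, or in what order, could follow the expected arm. Taking the primary outcome from records limits assessment bias but does not protect against this.

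**Working it through.** The documents give no figure for predictability, so there is none to reproduce.

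**Inputs.** Block sizes 2 and 4 (Appendix 5); 1:1 allocation stratified by centre (section 5.1, Appendix 5); 180 per centre (Appendix 5); every arm known locally in sequence (Appendix 4, steps 4 and 5). Assumption: the probability *w* that a block has size 2 is not stated, so it is varied from 0 to 1.

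**Guessing rule.** Whenever the arms at the centre are unequal, guess the arm that is behind; otherwise toss a coin. Completed blocks are balanced, so the running imbalance is that of the current block.

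**Block of 2.** Only the second place is unbalanced, and the guess is always right. Unbalanced places: 1. Correct guesses there: 1.

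**Block of 4.**
- Second place: always unbalanced, guess right with probability 2/3.
- Third place: unbalanced with probability 1/3, then certain.
- Fourth place: always unbalanced and certain.
- Unbalanced places: 1 + 1/3 + 1 = 7/3. Correct guesses there: 2/3 + 1/3 + 1 = 2.

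**Mixture, per block.**
- Mean length L = 2w + 4(1 − w)
- Unbalanced places U = w + (7/3)(1 − w)
- Correct guesses there C = w + 2(1 − w)
- Share guessable = U/L; accuracy when guessable = C/U; overall correct = [C + (L − U)/2]/L

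With w = 1/2: L = 3, U = 5/3, C = 3/2. Share = 5/9 = 55.6%; accuracy = 9/10 = 90.0%; overall = (3/2 + 2/3)/3 = 13/18 = 72.2%.

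| w (size 2) | Guessable | Accuracy when guessable | Overall correct |
|---|---|---|---|
| 1 | 50.0% | 100% | 75.0% |
| 2/3 | 54.2% | 92.3% | 72.9% |
| 1/2 | 55.6% | 90.0% | 72.2% |
| 1/3 | 56.7% | 88.2% | 71.7% |
| 0 | 58.3% | 85.7% | 70.8% |

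For a list of 180 at w = 1/2: 180 × 5/9 = 100 guessable allocations, of which 90 are guessed correctly. Adding half of the other 80 gives 130 correct, against 90 by chance.

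**Check.** A simulated guesser using the full history (180 per site, 3,000 replicates, w = 1/2) gave 55.5% guessable at 90.0% accuracy and 72.2% overall, with about 11% of allocations known with certainty.

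**Larger blocks, same rule.** Sizes 4, 6 and 8, equally likely: 63.8% guessable at 78.4% accuracy, 68.1% overall. The largest possible imbalance within a centre is half the largest block: 4/2 = 2 now, 8/2 = 4 with these sizes.

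**Neighbouring participants.** Take one block of 2 and one of 4. The expected number of adjacent opposite pairs is 1 + 3 × 2/3 + 2 × 1/2 = 4 of 6, or 67%. This holds for adjacent places on the whole centre list only. If participants fall at random to two Research Workers at a site, a worker's next own participant is in the opposite arm about 60% of the time; with three workers, about 57%.

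**The case against.** The person best placed to predict has no stated role before randomisation. Clinical Studies Officers draw up the list, and everyone on it is to be approached. Research Workers collect the baseline data and signal readiness; they are not told allocations, and they have separate offices, telephones and files. The Coordinator requests each allocation, but nothing says that the Coordinator is shown the running sequence. This stands. A reader might infer that facilitators steer enrolment or that concealment has failed, but the documents show neither. What remains is that the separation is implied by the order of steps and is nowhere stated as a rule.

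A reader might also infer that all site staff know the block sizes. The documents do not say who holds Appendix 5, and section 5.1 omits the sizes. They are nevertheless printed in the protocol, in a text marked as a draft.

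Nor do the documents support reading the 67% figure as the chance that one unblinding reveals a Research Worker's next participant. They describe the e-mail as concerning the worker's own participant, and the breach procedure implies more than one worker at a site. Any effect on rater blinding is secondary and small: the primary outcome comes mainly from records, and most secondary scales are self-reported or rated by clinical staff.

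Finally, larger blocks alone bring a modest gain: overall correct guessing falls only from 72% to 68%, and the guessable share rises. This too stands, so non-disclosure and separation of roles matter at least as much as block size.

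**Conclusion.** The point holds as a weakness of design and wording. Printed block sizes of 2 and 4, with a facilitator who sees both arms in sequence, would let a holder of that sequence guess about 56% of coming allocations at 90% accuracy, or 72% correct overall against 50% by chance. The 90% is an average over the guessable allocations and assumes equally likely sizes; over the whole range of mixes it runs from 86% to 100%, and the conclusion does not change.

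The figures also assume that one person sees the entire list for a centre in order and knows the sizes. They measure how far allocation could be predicted, and give no estimate of bias in the treatment effect. The concealment claimed in section 5.1 is not fully secured; that it was breached cannot be concluded.

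**What to change.** 1. Delete the block sizes from the protocol and its appended analysis plan, and keep them in a restricted trials-unit document.
2. For any remaining allocations, drop size 2 and use larger varying blocks that sites do not know, for example 4, 6 and 8.
3. State in section 5.1 that facilitators, and anyone else who sees allocations, take no part in identifying, approaching, consenting or ordering participants before randomisation.
4. If allocation is already complete, temper the concealment statements in section 5.1 and report who knew the sequence and the block sizes.

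The cost is a text edit, a setting in the randomisation system, and a possible imbalance of 4 instead of 2 in a centre of about 180. The current protocol version is dated May 2011 and the analysis plan August 2008. The documents do not show whether any allocations remain, so item 2 may no longer be possible; items 1 and 3, or item 4, do not depend on changing the system.
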